### Quantitative pre- and post- survey

The quantitative before and after survey will be administered pre (immediately before receipt of training), post (immediately following training) and follow-up (8–10 weeks after training) to both participant groups. Opportunity sampling will be employed, such that all eligible trainees within the study period (August 2025 to April 2026) will be invited to complete the surveys. Where possible, the trainer ([name]) or coordinator of the training (e.g., a key contact at the University) will send the pre survey to trainees around 1 week before training. A QR code to complete the pre survey will also be displayed on the first slide of the training, with time provided at the start of the training for trainees to complete it. At the end of the training, a QR code to complete the post-survey will be provided and all trainees will be asked to complete it. Trainees will be encouraged to complete the post survey before leaving the training site, or at least within the next 24 hours following training (although will be able to access the link at any time). Eight weeks after the training, the trainer or coordinator of the training will send trainees a link to complete the follow-up survey. Since training to VCSE service providers is often as part of mixed professional groups and to avoid isolation of VCSE service providers, all attendees of mixed groups containing VCSE service providers will be invited to complete the surveys. Using Gpower to calculate the total sample size required to detect a significant difference in confidence, perceived usefulness, perceived importance, and competence between trainee groups, to detect a small effect size (0.3) at 80% power, a minimum total sample size of 352 (176 in each group) is required to detect a significant difference in confidence and competence post training between participant groups (two groups t test (correlations not available to calculate for multiple linear regression), two tailed, p < .05). With an added 10% margin to account for missing data (that is not missing at random), the target sample size is 387 (194 per group). If the target sample size is not reached, the available data will be analysed acknowledging that the analyses was underpowered as a limitation. As secondary analyses, differences pre and post within each group will also be tested.

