Quantitative data will be analysed using SPSS [46]. To create a mean score for competency of ODQs and SMARTER goal facilitation, responses to the four scenarios for each skill will be aggregately coded by two independent coders (BN and another author), using established coding matrices adapted from previous studies [28]. Any discrepancies will be resolved through discussion with a third independent reviewer ([name]). Thus, aggregate scores (mean score across the four scenarios) will be calculated for both skills. Recall of the HCS philosophy will also be scored by two independent coders (BN and another author) and resolved through discussion with a third reviewer ([name]), using a self-created rubric available in the OSF pre-registration: https://osf.io/wpbn3/files. The data from attendees who are not undergraduate pharmacy students or service providers from the VCSE will not be included in the inferential analyses but will be summarised descriptively. Descriptive statistics will be produced for demographic characteristics, and pre and post scores relating to confidence, perceived usefulness, perceived importance, and competence (for both VCSE service providers and undergraduate pharmacy students). Exploratory baseline differences between professional groups for confidence, perceived usefulness, perceived importance, and competence will be tested through independent samples t-tests (or Mann-Whitney U tests if assumptions for an independent samples test are not met, tested using the Shapiro-Wilk test and Levene’s test for homogeneity of variances). Exploratory differences between trainee groups in post HCS ‘lite’ training (post survey) responses for perceived usefulness, perceived importance, and competence will be tested using a multiple logistic regression, controlling for baseline values (pre survey), age, and gender. Changes in confidence, perceived usefulness, perceived importance, and competence pre and post HCS ‘lite’ training will be tested within groups (conducted for both VCSE service providers and undergraduate pharmacy students) through within-subjects t-tests (or Wilcoxon Signed Rank tests If normality assumptions are not met, tested using the using Shapiro-Wilk test). Statistical testing will aid comparison with the existing literature of how HCS impact the confidence and competence of trainees across different settings. For the current realist evaluation, statistical testing will look to test (refine, support, refute) the IPTs, and therefore analysis will look to ‘preserve’ the configurations in analysis. For example, comparison across participant groups (undergraduate pharmacy students and VCSE service providers) will be tested for a relationship with proposed outcomes (motivation, competence, and confidence). If quantitative variables do not meet normality assumptions, non-parametric tests will be applied.

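### The post-training group comparison is specified as a logistic regression, but its outcomes are scores and the sample size rests on a t test with linear regression in mind

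*Protocol article*

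**What the plan says.** All the relevant text is in the protocol article, section Quantitative pre- and post- survey.

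- **Sample size paragraph.** The between-group comparison is sized "to detect a small effect size (0.3) at 80% power", using a "two groups t test (correlations not available to calculate for multiple linear regression), two tailed, p < .05". The result is that "a minimum total sample size of 352 (176 in each group) is required". The paragraph names confidence, usefulness, importance and competence, then confidence and competence after training. It calls the within-group pre/post tests secondary.
- **Analysis paragraph, scoring.** For competence, "aggregate scores (mean score across the four scenarios) will be calculated for both skills".
- **Analysis paragraph, model.** The post-training comparison between trainee groups, labelled exploratory and covering usefulness, importance and competence, "will be tested using a multiple logistic regression, controlling for baseline values (pre survey), age, and gender". Confidence is not in this sentence.
- **Analysis paragraph, other tests.** Confidence, usefulness, importance and competence are compared at baseline with independent t-tests (Mann-Whitney if Shapiro-Wilk or Levene checks fail). Within groups they are compared with paired t-tests (Wilcoxon if normality fails).
- **Analysis paragraph, last sentence.** "If quantitative variables do not meet normality assumptions, non-parametric tests will be applied".

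**The concern.** The section points to two different models for one comparison. The sample size paragraph assumes a difference in mean scores and refers to linear regression; the analysis paragraph names logistic regression. Competence is explicitly a mean, and t-tests with normality and variance checks make sense only if the other outcomes are also quantitative scores. A binary logistic model needs a two-valued outcome. Nothing in the article turns these scores into one: it gives no threshold, no responder definition and no ordinal model.

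An analyst following the text would have to choose a cut-point after the plan was fixed, or decide that the word was not meant. The first choice changes the question from a mean difference to the odds of exceeding a threshold, leaves room for a data-driven cut, and departs from the basis of the power statement.

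Two loose ends belong to the same edit. Confidence is part of the sample size statement but has no post-training between-group model. The closing fallback sentence is not limited to the t-tests, which already have their own fallbacks. The only between-group non-parametric test named is Mann-Whitney, which takes no covariates. The groups are not randomised, and the Introduction and Discussion expect them to differ, so the baseline adjustment should not be open to removal by a normality test.

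**Working it through.** **1. Inputs.** From the sample size paragraph: standardised difference 0.3, power 80%, two-sided 0.05, 176 per group, target 194 per group after a 10% margin. Assumed, because the article gives no values: normal scores with equal SD (set to 1), cut-points from 50/50 to 10/90, and baseline–post correlations from 0 to 0.5.

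**2. The stated sample size.** Normal approximation: n = 2(1.9600 + 0.8416)² / 0.3² = 2 × 7.849 / 0.09 = 174.4, so 175 per group. The noncentral t gives 175.4, so 176 per group and 352 in total. At 176 per group the noncentrality is 0.3 × √(176/2) = 2.81 on 350 df, and power is 80.1%. With the margin, 176 × 1.1 = 193.6 and 352 × 1.1 = 387.2, matching 194 and 387. At 194 analysed per group, power is 83.8%. The plan's figure reproduces for a t test on a score.

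**3. Which model fits the text.**

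| Element | Implied outcome type |
|---|---|
| Sizing by two-group t test, linear regression mentioned | quantitative |
| Competence as a mean over four scenarios | quantitative |
| t-tests with Shapiro-Wilk and Levene checks | quantitative |
| Multiple logistic regression | categorical |

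Only the last row disagrees.

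**4. If the scores were dichotomised (unadjusted).** Put the group means at ±0.15 and cut at c. The proportions above the cut are p₁ = 1 − Φ(c + 0.15) and p₂ = 1 − Φ(c − 0.15). With p̄ their average,

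power = Φ{ [p₂ − p₁ − 1.96 √(2p̄(1 − p̄)/n)] / √([p₁(1 − p₁) + p₂(1 − p₂)]/n) }.

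Median split, n = 176: p₁ = 0.4404, p₂ = 0.5596, difference 0.1192. The numerator is 0.1192 − 1.96 × √(0.5/176) = 0.1192 − 0.1045 = 0.0147. The denominator is √(0.4929/176) = 0.0529. The ratio is 0.28, so power is 61%.

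| Share above cut | p₁ v p₂ | Power, 176/group | Power, 194/group | n/group for 80% |
|---|---|---|---|---|
| 50% | 44.0% v 56.0% | 61% | 65% | 275 |
| 30% | 24.8% v 35.2% | 57% | 61% | 306 |
| 20% | 15.8% v 24.2% | 50% | 54% | 362 |
| 10% | 7.4% v 12.6% | 37% | 40% | 526 |

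**5. With baseline adjustment (simulation, 176 per group).** There were 1,000 runs per row for the linear and binary models and 200 for the five-level ordinal model.

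| Assumed baseline correlation | Linear | Logistic, median split | Logistic, upper fifth | Ordinal logistic |
|---|---|---|---|---|
| 0 | 81% | 64% | 52% | 74% |
| 0.3 | 84% | 64% | 50% | 80% |
| 0.5 | 91% | 70% | 57% | 86% |

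The simulation margin is about 1.96 × √(0.64 × 0.36/1000) = 3 points for the binary model and about 6 points for the ordinal one. The 3-point gap between 64% here and 61% in step 4 at zero correlation is therefore about the size of simulation error, not a gain from adjustment. Both groups were given the same baseline distribution, and age and gender were left out. Imbalance between the groups would cost any adjusted model some precision, by an amount the article gives no data to judge.

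**The case against.** The strongest reply is that this is a slip of one word. The sample size paragraph refers to linear regression, so an informed reader would take "logistic" to mean "linear"; nothing would then be dichotomised and power would be kept or improved. This is plausible, and it limits what can be claimed. A reader might infer that the scores must be dichotomised and that the 80% power is lost. The article does not support that: it plans no cut-point, an ordinal logistic model would need none, and the 80% is correct for the test it was computed for. Putting group on the left-hand side would also avoid a cut, but the article does not propose it, and its coefficient would not be a difference in post-training scores.

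The second reply is that the comparison is labelled exploratory, that the Triangulation section says the survey does not specifically test the programme theories, and that the interviews carry the explanation. That is fair, and calling it the study's main analysis would go too far. It is still the comparison on which the survey is sized, and the Discussion names reaching that size as the main anticipated challenge.

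Third, the fallback sentence names no test and does not say that covariates are dropped. Mann-Whitney is tied to the baseline t-tests and Wilcoxon to the paired ones. So the sentence is ambiguous; it does not clearly remove the adjustment. A reader might go on to infer that normality checks would almost always fail on rating items, or that age would nearly separate the two groups. The article gives neither the rating scales nor any age data, so neither inference has support.

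Finally, only competence is expressly a mean score. For usefulness and importance, quantitative scoring is inferred from the tests applied; the items are in the pre-registration, which is not shown.

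**Conclusion.** The model named for the post-training comparison contradicts the sample size paragraph and does not suit the outcomes as the article describes them. That much rests on the text alone. The loss of power is conditional on a binary logistic model actually being run. At 176 per group and a standardised difference of 0.3, power would then drop from 80% to about 61% at a median split (about 64–70% with baseline adjustment), and to 37–57% unadjusted at the more unequal cuts tried. A linear model would give about 80–91% over the same assumed correlations. These figures assume normal scores, equal SDs and similar baseline distributions in the two groups. The stated sample size needs no change on this account. This is a correction to the wording of the analysis, and it should be made before the data are analysed because the text as it stands leaves the model to be guessed.

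**What to change.** 1. Replace the logistic regression with a multiple linear regression (ANCOVA) of post score on group, baseline score, age and gender, reporting the adjusted mean difference between groups with its 95% confidence interval.
2. Add confidence to the outcomes in that sentence, to agree with the sample size paragraph.
3. State that the closing non-parametric fallback applies only to the unadjusted t-tests, so that a failed normality check cannot replace the baseline-adjusted comparison with an unadjusted one.
4. If a logistic model was truly intended, say whether it is ordinal or binary, fix any cut-point in advance, and base the power statement on that model.

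The cost is a few sentences, with no extra data and no change of software, since SPSS fits this model. The pre-registration should be checked for the same wording and given a dated amendment if it has it. The Methods put the end of data collection at July 2026 and results at March 2027, so on that timetable the change can be made before analysis.

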
### Qualitative realist interviews

Qualitative semi-structured and theory driven realist interviews will be conducted with undergraduate pharmacy students and VCSE service providers who have received receipt of HCS ‘lite’ training. In accordance with a realist approach [47], purposive sampling will be applied to sample participants from a broad range of contexts identified as relevant from the IPTs (e.g., types of role within the VCSE, interval since receipt of HCS ‘lite’ training). The purposive sampling approach will also be iterative depending on relevant contexts that emerge throughout the interviews. Participants will be recruited via two sources; those who complete the expression of interest form after the follow-up survey, and through contacting previously trained pharmacy students and VCSE service providers. In accordance with a realist approach which focuses on explanatory depthbased on coherence and credible causality, defining the sample size a priori for each participant group was not possible [47,48]. However, to assist with funding acquisition for the project, information power [49] was applied to provide an estimate of the target sample size for each participant group. The aim is specific and the lead researcher (BN) is an experienced qualitative interviewer, although this must be balanced with the possibility of convenience sampling depending on interest and that the analysis will test programme theories, which would both require a larger sample size. Thus, the estimated sample size is 40 (n = 20 per professional group), although the exact final sample size and characteristics of the sample will be developed iteratively.

Topic guides have been structured around the IPTs, seeking to test and refine them whilst also being open to emergent programme theories. As is distinctive with realist interviews, interviews (guided by the topic guide) will adopt a teacher learning cycle, whereby the researcher (BN) shares their initial theorising (most often parts of their IPTs in lay terms) and asks the participant to share their thoughts [48]. Participants become the teacher by sharing their own thoughts out how HCS training worked for them [48]. One topic guide has been developed for each participant group (VCSE service providers and undergraduate pharmacy students), given that the overall programme theories differ between groups. Broadly, both topic guides cover the context in which participants work, how they engaged with the training, experienced the training, and applied and embedded the training. Again, in accordance with a realist approach the content of the topic guide will be iterative, to reflect the evolving programme theories. Both initial topic guides are available on the OSF pre-registration (https://osf.io/wpbn3/files).

Participants will be sent the consent form for interviews following receipt of the information sheet and asked to return written consent prior to the interview. Thus, informed written consent will be gained. Interviews will be offered online via Teams but may also be conducted in person if needed. At the start of the interview, consent will be confirmed verbally. Interviews will likely last between 30–60 minutes and will be audio recorded (if in-person) or recorded in-app (if on Teams). Participants that take part in an interview will be renumerated with a £20 shopping voucher for approximately one hour of their time. Recordings will be sent to a transcription service for transcription, then anonymised by the lead author (BN). In accordance with open science practices, anonymised transcripts will be made publicly available via the UK Data Service, providing participants provide their consent.

The data will be analysed iteratively to test, refine, and add to the IPTs using CMO configurations. Transcripts will firstly be imported into NVivo Version 12 [50] for analysis. The planned data analysis approach within Nvivo has been adapted from existing guidance [51], and may be further amended once data analysis begins. Data coding will be organised by IPTs, through creating a node for each IPT. Emerging programme theories will be added with new nodes. Analysis will preserve dyads and triads of CMO configurations to ensure a coherent analysis. Codes to organise data within each node (programme theory) will be developed iteratively, but will distinguish whether the data supports of refutes it. Subsequently, the writeup will distinguish between unsubstantiated (there was no relevant data relating to that IPT) and discounted (there was data refuting that IPT) programme theories. Mind mapping (e.g., using Miro) and editing of the existing overall programme theories will be utilised to develop causal understanding throughout analysis. Analysis will be conducted by the lead author (BN) although updates to programme theories will be discussed with the research team and stakeholders [48,52]. Changes to the IPTs throughout the analysis will be documented using linked Memos, using highlighting for new additions and strikethroughs for deletions. Again, substantive/formal theory will be utilised to assist with explanatory understanding. Theories will be sourced through the existing list created during IPT development, conversations with experts (all authors), and further literature searching. Inferences will be drawn from the depth and richness of the data in informing programme theories and the coherence and credible causality provided by the programme theories themselves.

Following existing guidance for realist evaluations [48], several quality assurances will be adopted. Given that realist interviewing should be informed by naturalistic observation, the lead author observed HCS ‘lite’ training which informed the initial development of IPTs. Although repeat interviews will not be feasible given the existing requirement of repeated surveys, the lead author (BN) will instead encourage participants to email if they develop any further theories after the interview.

### Triangulation

The survey will not specifically test IPTs but will provide validation of the proposed outcomes, organised broadly by context of trainees (comparing VCSE service providers and undergraduate pharmacy students). The qualitative data will instead link the outcomes identified within the survey to context and mechanisms. Both streams of data will be triangulated through ‘qualitising’ (transforming into qualitative data) the quantitative survey data [53]. Namely, C, M, or O (most likely) statements of configurations will be generated, generating dyads of CMO configurations where possible (e.g., that a specific context leads to a specific outcome). These will be added as a file into Nvivo and coded in the same way as the transcripts (as provided above), so that the quantitative data can be fully incorporated into the qualitative analysis.

### Optimising involvement, inclusion, and engagement

Realist methods are grounded in a pragmatic aim of policy change [54]. Thus, accessing individuals with relevant insights and translating the findings into policy ad practice is arguably even more central and important than for other methods. Optimising inclusion of individuals with relevant insights was considered. HCS ‘lite’ training is delivered in the English language across Portsmouth, so the evaluation assumes a fundamental understanding of the English language of participants. Thus, translation services will not be available. Paper copies of the survey will be available to trainees during HCS ‘lite’ training. Dissemination of the study findings will aim to utilise a range of formats for accessibility, including an animation. Stakeholder involvement will further inform appropriate dissemination strategies.

### Knowledge translation

As this study was co-designed with author [name], the findings of this evaluation will directly inform the approach to HCS adopted across Portsmouth. Additionally, involvement of key decision makers has created ownership of the project which will facilitate impact. Authors BN, [name], and CH are also established researchers of MECC subsequently have developed connections with other implementors of MECC nationally. These existing networks will be utilised to disseminate the findings to other regions, to help them consider their approach to MECC training. Furthermore, the findings of the current evaluation aim to inform a future effectiveness study of MECC delivery, through providing HCS training. It was first necessary to ensure that HCS enables all trainees to deliver MECC conversations.

## Discussion

This realist evaluation will produce a refined programme theory which explains how and why a specific approach to MECC training, HCS, works, including how it works differently for different audiences and thus how it might need to be adapted to ensure that all trainees are equipped equally to deliver MECC conversations. By including both undergraduate pharmacy students and VCSE service providers, this study will enable comparison based on a number of potentially important contextual factors. VCSE service providers do not work in a healthcare setting and may not have a healthcare background or any prior knowledge of health promotion, so may not view MECC as relevant to them [30]. However, they often have highly diverse specialist backgrounds and are experienced and confident in talking to service users, strongly driven by a desire for social good [30]. Meanwhile, undergraduate pharmacy students are trained as healthcare professionals, including to deliver healthy lifestyle advice, with health promotion now considered a key part of a Pharmacist’s role [55]. However, undergraduate pharmacy students may have had little experience of interacting with service users and have chosen to study pharmacy for a range of reasons [56]. The realist evaluation allows for these contextual differences to be incorporated into the analysis, to provide further understanding about what elements of HCS work for whom and why. The findings will be published in a peer reviewed journal, submitted prior to April 2027. Additionally, the findings will be disseminated with key stakeholders (including the stakeholder involvement group for this study), providing recommendations to optimise impact of the evaluation.

The main anticipated challenge for the study is achieving the target sample size for the quantitative surveys, to reach sufficient statistical power to detect for significance. However, differences pre and post HCS ‘lite’ training can still be tested for within-groups with a smaller sample, which can be narratively compared between participant groups. Equally, the main strength of this study is that it has been co-produced between research and practice, making knowledge translation more likely. This context has maintained a pragmatic focus for the current evaluation. For example, visual depictions of programme theories are essential to communicate the findings with individuals outside of research settings. The challenge of co-production approaches is maintaining the collaboration [57], which has been facilitated within this project by in-person research visits. One limitation is that given that the study was not specifically designed to test programme theories, the quantitative data will not statistically test CMO configurations. Whilst the two participant groups will allow for significant differences in outcomes between groups of trainees to be tested, the IPTs highlight that the context is far more nuanced than occupation or job role. The qualitative data will thus be essential in configuring the outcomes identified in the survey with their respective context and mechanisms. Similarly, whilst an eight-week follow-up period (selected as sufficient to demonstrate habit formation [58]) may limit conclusions that can be drawn about how HCS training is embedded over time, the interviews will inform this objective by including participants from a broad range of durations from receiving HCS training.

Nevertheless, the key target outcome of the current realist evaluation is to inform approaches to MECC training across the UK and beyond. Ensuring that MECC training is effective in helping people to deliver MECC conversations may help to create a culture around health promotion and prevention. There is currently no specific guidance about how MECC training is delivered, indicating the potential for policy-level impact of the current study. For example, if HCS is demonstrated to increase confidence and competence no matter the background of trainees, there is rationale for MECC policy to specify HCS training as the approach to MECC delivery. Alternatively, both approaches may instead complement each other, providing a rationale to include elements of both. MECC is also unique in that it raises the possibility of health promotion outside of healthcare settings, opening new opportunities to prevent disease. Due to trusting relationships within the VCSE, there is rationale that MECC within the VCSE may be more impactful than when delivered in other settings (e.g., healthcare) where the service provider is not known to the service user. Assessing whether HCS ‘lite’ training is sufficient to enable service providers from the VCSE to deliver MECC is the first step to evaluating the impact of MECC within the VCSE. Also, by utilising existing measures to assess the change in confidence, motivation, and competence following HCS ‘lite’ training, the results of the survey will contribute to the existing literature supporting HCS ‘lite’ training, and aid comparison between other trainee groups (e.g., staff at Sure Start children’s centres, physiotherapists) [23,31]. Thus, the current study will provide a holistic understanding of what elements of HCS training work for whom, under what circumstances, in what respects, to what extent, and why, and in the process informing the same questions about MECC training overall.

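### If recruitment falls short, separate within-group pre/post tests compared in words cannot show whether the two trainee groups differ; the adjusted between-group estimate with its interval should carry that claim

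*Protocol article*

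**What the plan says.** The Discussion of the protocol article names the risk: "The main anticipated challenge for the study is achieving the target sample size for the quantitative surveys". It then reassures the reader that pre/post differences can still be "tested for within-groups with a smaller sample, which can be narratively compared between participant groups". No between-group estimate, interval or interaction is attached to that comparison.

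The section on the quantitative pre- and post-survey gives the method. "Changes in confidence, perceived usefulness, perceived importance, and competence pre and post HCS ‘lite’ training will be tested within groups", by a paired t-test or a Wilcoxon signed rank test in each group separately. The same section calls these tests secondary.

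Two other statements in that section bear on the point. On a shortfall: "If the target sample size is not reached, the available data will be analysed acknowledging that the analyses was underpowered as a limitation". The section also plans a regression of post-training scores on trainee group, adjusted for baseline, age and gender. This covers perceived usefulness, perceived importance and competence. Confidence is not in its list, although it is among the outcomes named in the sample-size paragraph.

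**The concern.** The survey was sized for the comparison of voluntary-sector (VCSE) providers with pharmacy students. When that comparison loses power, the Discussion points the reader to two within-group tests set side by side. A significant change in one group and a non-significant change in the other is not evidence that the groups differ. Two significant changes are not evidence that they respond to the same degree.

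A wrong reading would travel. Under the Triangulation section, survey results become statements about context and outcome, with context organised broadly by trainee group, and are coded alongside the interview transcripts. A spurious finding that training worked in one group and not the other could enter the programme theory that way. So could a false impression that both groups respond alike.

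**Working it through.** **The plan's own figure.** Inputs from the sample-size paragraph: "to detect a small effect size (0.3) at 80% power"; "two tailed, p < .05"; two independent groups of equal size. The exact two-sample t calculation gives 175.4 per group. Rounded up, this is 176 per group and 352 in total, with power 0.801. The stated figure, "a minimum total sample size of 352 (176 in each group) is required", reproduces. It is not in dispute.

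**Assumed inputs.** The protocol gives neither a within-group effect size nor a shortfall sample size. I write dz for mean change divided by the SD of change, take 0.3, 0.5 and 0.8, and use group sizes of 60 v 60, 150 v 40, 50 v 50 and 100 v 100. All of these are illustrative.

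**Formulas.** The power p of each paired t-test comes from the noncentral t distribution with n − 1 degrees of freedom and noncentrality dz × √n, two-sided 0.05. The groups are independent, so:
- P(exactly one significant) = p1(1 − p2) + p2(1 − p1)
- P(both significant) = p1 × p2

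**Case 1: the same true change in both groups.**

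| dz | Group sizes | p1 | p2 | Exactly one significant |
|---|---|---|---|---|
| 0.3 | 60 v 60 | 0.628 | 0.628 | 2 × 0.628 × 0.372 = 0.47 |
| 0.3 | 150 v 40 | 0.955 | 0.457 | 0.955 × 0.543 + 0.457 × 0.045 = 0.54 |
| 0.5 | 60 v 60 | 0.968 | 0.968 | 2 × 0.968 × 0.032 = 0.06 |
| 0.5 | 150 v 40 | >0.999 | 0.869 | 0.13 |
| 0.8 | 60 v 60 | >0.999 | >0.999 | <0.001 |
| 0.8 | 150 v 40 | >0.999 | 0.998 | 0.002 |

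A direct test of the difference would be wrong in 5% of studies in every row.

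**Case 2: a real gap, dz 0.8 in one group and 0.5 in the other.**
- 50 per group: >0.999 × 0.934 = 0.93 both significant.
- 100 per group: >0.999 × 0.999, so over 99% both significant.

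The gap of 0.3 equals the planning effect only if the pre/post correlation is 0.5. The SD of change is the SD of the score times √(2(1 − r)), which equals the SD of the score at r = 0.5. At r = 0.7 a between-group d of 0.3 becomes 0.3/√0.6 = 0.39 on the dz scale.

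**What the direct comparison offers at the same sizes.** For d = 0.3, unadjusted, power is 0.32 at 50 per group, 0.56 at 100 per group and 0.39 at 150 v 40. The 95% interval half-widths, t × √(1/n1 + 1/n2), are 0.40, 0.28 and 0.35 SD. Power is low, but the uncertainty is visible and the error rate is controlled.

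**The case against.** The strongest reply is that nothing has been replaced. The methods say the available data will be analysed with low power acknowledged. The adjusted between-group regression carries no condition on sample size, the within-group tests are labelled secondary, and the Discussion remark is permissive. This stands. A reader might infer that the narrative comparison takes over from the direct test on a shortfall, but the text does not say so. What remains is that the remark offers the narrative comparison as the remedy for lost between-group power, without saying that it cannot do that job. Confidence has no place in the regression list either; a later example sentence in the same section mentions testing trainee group against confidence, but specifies no adjusted model for it.

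A reader might also infer that the policy passage in the Discussion, "if HCS is demonstrated to increase confidence and competence no matter the background of trainees", commits the same error. It does not: it speaks of an increase in each group, not an equal one, and within-group changes bear on that. It should not be charged here. Nor is there reason to require that the interval exclude differences of 0.3 or more. That would be an equivalence criterion the study was not designed to meet: with a true difference of zero and no covariate gain, the chance of meeting it is about 61% at 176 per group and 13% at 100.

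The narrative might compare magnitudes and not significance labels, since descriptive pre and post scores are planned for both groups. That would be milder. But the sentence speaks of differences being tested and promises no interval for the gap between groups.

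Finally, the plan intends to sample the groups evenly, so 150 v 40 is only an illustration. The problem does not depend on it: 60 v 60 gives 47% at dz 0.3.

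**Conclusion.** The point holds in limited form. The Discussion offers an inference that separate within-group tests cannot support, beside a direct comparison that is still planned. Under the assumed values, the risk of a false difference is about one in two for small changes (47% to 54% at dz 0.3), modest at dz 0.5 (6% to 13%), and negligible for large changes. Where changes are large, the opposite error takes over: both groups are significant in 93% to over 99% of studies despite a gap of 0.3. Which error is likelier depends on within-group effects that the protocol does not give. The stated sample size is correct, and the point concerns only how a shortfall would be interpreted.

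**What to change.** In the Discussion, replace the narrative comparison with a statement along these lines: at any achieved sample size, the baseline-adjusted difference between trainee groups, with its 95% confidence interval, is the only basis for saying that the groups differ or respond alike; within-group changes are reported as descriptive estimates with confidence intervals.

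In the survey analysis section, add confidence to the outcomes of the adjusted between-group analysis. That section calls the model logistic, while the sample-size paragraph refers to linear regression. The two should be reconciled so that the analysis yields a difference in scores.

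The cost is a few sentences and one more outcome in a planned model; no further data are needed. The downside is that conclusions about group differences will be less definite if recruitment is low.
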